### Allocation

The allocation ratio of participating hospitals is set to 1:1 with unequal cluster sizes. In order to achieve similar clusters between the FLS-CARE and control groups, the hospitals are stratified by type (local/regional and superregional trauma centre) and location according to a simplified classification (metropolis yes/no). To eliminate selection bias, the trust centre of the evaluating institution of the study (LMU-HSM) was included in the sequence generation process to pseudonymise (conceal) all potential trauma centres before randomisation into FLS-CARE and control groups. The randomisation was performed by LMU-HSM using R 3.3.2.

Owing to the nature of the study, blinding of neither the study participants nor the FLS-CARE/study nurses is feasible.

### Data collection

All participants are interviewed at five points in time (see Table 1 and Fig. 1): directly after informed consent (t_0_), at discharge (t_1_), after 3 months (t_2_), 12 months (t_3_) and 24 months (t_4_) post fracture. For the FLS-CARE group, outcomes are collected by either outpatient physician or FLS-CARE nurses at the follow-up appointments (t_1–4_). Both outpatient physician and FLS-CARE nurse receive prior training in data collection from the FLS-CARE study group. For the control group, study nurses are responsible for data collection.

All follow-up appointments and outcomes are recorded in the specifically developed and highly standardised FLS-CARE tailored IT-based documentation, so-called FLS-CARE documentation modules, to promote data quality.

The FLS-CARE/study nurses also have access to diagnostic, therapy and process data through the aforementioned FLS-CARE documentation modules. They can monitor whether participants comply with follow-up schedules. If a patient does not appear at an appointment, the FLS-CARE/study nurse receives notification and can contact him or her by telephone. If he or she cannot or does not want to attend the follow-up appointment due, the FLS-CARE/study nurse tries to collect the study parameters by telephone.

Participation is not specifically promoted in the intervention group, other than mentioned above, in order to create results that are directly transferable to clinical routine. Missing data and related information are recorded as such in the FLS-CARE documentation modules.

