#### Intervention group

The FLS-CARE study intends to reduce the frequency of secondary fractures by targeting underlying osteoporosis as the root cause. The study programme includes a guideline-based care concept (FLS) in a network of multiple professionals (physicians, nurses and physiotherapists) from the inpatient and outpatient sectors. Specially trained FLS-CARE nurses play a central role in FLS-CARE as liaison partners for the sectors. They are responsible for guidance between hospital and ambulatory care and health literacy of the patients. They monitor patients’ adherence and ensure the conduct of intervention measures. The FLS-CARE nurses at the study centres, the participating GPs and medical specialists are educated on the principles of FLS and parameter collection for the study.

The FLS model for the patients of the FLS-CARE (intervention) group comprises four main modules:
*Diagnostics*: All patients receive an evidence-based diagnostic assessment based on the DVO guidelines [11] and the best practice framework of the IOF [12] during their hospital stay.*Education*: The FLS-CARE nurses highlight the importance of, for example, fall prevention and other physiotherapeutic exercises and motivate patients to follow up their goals for therapy to prevent secondary fractures and to enhance health literacy and behaviour. After discharge, the FLS-CARE nurses make domiciliary visits to assess and educate patients on individual fall risks. They also highlight the nearest support groups for patients suffering from osteoporosis as additional resources.*Therapy*: All patients receive medical and physical therapy as indicated, again in accordance with DVO and IOF guidelines. Treatment plans and adherence are regularly monitored by the FLS-CARE nurses.*Coordination*: The FLS-CARE nurses help to coordinate physical therapy sessions and follow-up appointments (3, 12 and 24 months post fracture) in the outpatient sector at certified GPs and/or medical specialists to ensure the continuity of specific care. In regular telephone calls, FLS-CARE nurses try to improve long-term adherence to therapy.

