#### Control group

Participants in the control group will receive treatment as usual with follow-up appointments at identical intervals to the FLS-CARE group. Trained study nurses are responsible for contacting the patients and collecting study parameters from the control group to avoid potential biases.

All trauma centres treating the control group are prohibited from implementing any form of FLS during the study period to avoid potential bias. However, they are not forbidden to practise modules of FLS if they have already been implemented as a standard of care.

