**Table 1 Tab1:**
[figure not shown]
Schedule of enrolment, intervention and assessments

** Follow-up dates refer to date of initial fracture*

Process indicators relate to the medical and diagnostic guideline adherence of all participants and are derived from the documentation of FLS-CARE/study nurses as well as insurance claims data from the participating sickness funds. Additionally, contextual factors that facilitate or hinder the intervention and mechanisms of impact are identified through semi-structured interviews and questionnaires with relevant stakeholders in accordance with the Medical Research Council (MRC) guidance on process evaluation of complex interventions [15]. Parameters for the economic evaluation of the health care programme, next to the secondary fracture rate (effectiveness measure) and QALYs (utility measure), include implementation costs of FLS-CARE and overall treatment costs associated with the initial hip fracture from sickness fund data. Risk factors of secondary fractures and potential confounders of the treatment effect are collected using the Charlson Comorbidity Index (CCI), Elixhauser Comorbidity Index (ECI) and the fracture risk assessment tool of the IOF (FRAX®).

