### Sample size

Sample size calculation is based on the comparison between the primary endpoint of the FLS-CARE group versus the control group in patients with femoral fragility fractures. Johansson et al. (2017) investigated the follow-up rate in severe osteoporotic fractures in a large study and found that the secondary fracture rate was 26% [16]. However, the exact follow-up period in which the secondary fractures occurred was unclear. In a study by Johnell et al. (2004) [17], a secondary fracture rate of 10% was observed in patients (mean age 80 years) with hip fractures 2 years after the initial fracture. Thus, this rate was assumed to approximate the value for the present control group. Following the method of Hemming et al. (2011) [18] for cluster-randomised studies with unequal cluster sizes, the number of cases per group for a given number of clusters can be determined as follows:
$$ {n}_C=\frac{n_ik\left[1-\rho \right]}{\left[k-{n}_i\left({cv}^2+1\right)\rho \right]}. $$where *n*_*i*_ corresponds to the individually randomised sample size, *k* to the number of clusters per group, *cv* to the coefficient of variation of a cluster and *ρ* to the intra-cluster correlation.

The participating hospitals are considered as cluster units. For the calculation of the number of patients needed for the analysis, 9 hospitals per group, an intra-cluster correlation of 1% and a coefficient of variation of clusters of 1.37 were assumed. Based on these values, 507 patients are needed per group to find a significant difference of 7% in the secondary fracture rate 2 years after the initial fracture (FLS-CARE group = 3% and control group = 10%) with a power of 80% and a significance level of 5%. The sample size was calculated using GPower 3.1 and R 3.3.2.

In the FAITH study (2014) [19], two surgical methods and their outcome after 2 years were studied in patients with fragility hip fractures. For sample size calculations, a mortality rate of 10% after 2 years and a lost to follow-up rate of 5% were taken into account. Owing to comparable patient populations regarding age and injuries, a similar drop-out rate is assumed for the FLS-CARE study. However, it is expected that the lost to follow-up rate will be 10%, especially in the control group. These considerations result in a total drop-out rate of 20% and a total number of 1216 patients (608 patients per group distributed over 9 clusters).

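### Fractures are ascertained by unblinded intervention staff in one arm and by separate unblinded study nurses in the other, and the article names no arm-neutral source for the primary outcome

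*Protocol article*

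**What the plan says.** The primary outcome is the secondary fracture rate at 24 months, and falls are a secondary outcome (Protocol article, Outcomes). On who records outcomes, Data collection says "For the FLS-CARE group, outcomes are collected by either outpatient physician or FLS-CARE nurses at the follow-up appointments", and then "For the control group, study nurses are responsible for data collection". The Control group section presents the separate staff as a safeguard: "Trained study nurses are responsible for contacting the patients and collecting study parameters from the control group to avoid potential biases". The Allocation section states that "blinding of neither the study participants nor the FLS-CARE/study nurses is feasible".

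The Intervention group section shows that the FLS-CARE nurses also deliver the programme. They educate patients, visit them at home to assess fall risk and monitor adherence, and "In regular telephone calls, FLS-CARE nurses try to improve long-term adherence to therapy". No such contacts are described for controls. Sample size adds that "it is expected that the lost to follow-up rate will be 10%, especially in the control group".

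The article also describes measures that limit differences between arms. Follow-up intervals are the same, collectors are trained in both arms, and a missed appointment prompts telephone collection in both arms. A common system is used: "All follow-up appointments and outcomes are recorded in the specifically developed and highly standardised FLS-CARE tailored IT-based documentation".

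Claims data appear in two places. Process indicators for all participants are "derived from the documentation of FLS-CARE/study nurses as well as insurance claims data from the participating sickness funds" (text with Table 1), and treatment costs come from sickness-fund data (same text, and Economic evaluation). Insurance with a participating fund is an inclusion criterion. The visible text names no claims source, blinded assessor or adjudication for fractures or falls.

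**The concern.** In an unblinded trial, the main protection for an event outcome is to ascertain it the same way in both arms. Here the recorder is tied to the arm. In one arm it is the nurse whose programme is being tested, or an outpatient physician. In the other it is a study nurse with no part in the programme. Contact also differs: a patient with home visits and coaching calls has more occasions to mention a fracture or a fall.

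The two mechanisms pull in opposite directions. More contact tends to find more events under FLS-CARE and would hide a benefit. Reluctance to record failures of one's own programme would create a benefit. Heavier loss among controls adds missing outcomes in that arm. Multiple imputation, which the article plans, can address a missing value but not a fracture recorded as absent. If capture differs, the primary comparison mixes a treatment effect with a detection effect, and neither a positive nor a null result can be read cleanly.

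**Working it through.** **Inputs from Sample size:** control 10%, FLS-CARE 3%, 80% power, 5% significance, k = 9 clusters per group, ρ = 0.01, cv = 1.37, 507 per group for analysis.

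**Inputs assumed:** capture, meaning the share of true fractures that is recorded. The document gives no such figure, so a range is shown.

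**Step 1. Reproduce the plan's figure.** The two-proportion formula (two-sided, pooled variance, no continuity correction) gives n_i = 194. The protocol's cluster formula then gives

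n_C = 194 × 9 × 0.99 / [9 − 194 × (1.37² + 1) × 0.01] = 505.6, so 506 against the stated 507. The figure reproduces.

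**Step 2. Effective size.** Mean cluster size is 507/9 = 56.33. The design effect is 1 + [(1.37² + 1) × 56.33 − 1] × 0.01 = 2.611. The effective size is 507/2.611 = 194.2 per group.

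**Step 3. Method for power.** SE = √{[p_C(1 − p_C) + p_F(1 − p_F)]/194.2} and δ = (p_C − p_F)/SE. The normal approximation is Φ(δ − 1.96). The t version uses a noncentral t with 18 − 2 = 16 df (critical value 2.120), which reflects the small number of clusters.

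**Step 4. True effect of 10% against 3%, with incomplete capture.**

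| Capture FLS-CARE / control | Recorded rates | Difference | Power, t (16 df) | Power, normal |
|---|---|---|---|---|
| 100% / 100% | 3.00% v 10.0% | 7.00 points | 76% | 81% |
| 95% / 85% | 2.85% v 8.5% | 5.65 points | 62% | 68% |
| 100% / 90% | 3.00% v 9.0% | 6.00 points | 65% | 71% |
| 100% / 80% | 3.00% v 8.0% | 5.00 points | 53% | 58% |
| 100% / 70% | 3.00% v 7.0% | 4.00 points | 40% | 44% |

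For the second row, SE = 0.0233 and δ = 0.0565/0.0233 = 2.42. The first row shows 81% rather than 80% because the variance here is unpooled; the pooled version gives 80%.

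**Step 5. No true effect (10% in both arms), with lower capture under FLS-CARE.**

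| Capture FLS-CARE / control | Recorded rates | Risk ratio | Chance of a significant result favouring FLS-CARE, t / normal |
|---|---|---|---|
| Equal | equal | 1.00 | 2.5% / 2.5% |
| 85% / 95% | 8.5% v 9.5% | 0.89 | 5.1% / 5.3% |
| 90% / 100% | 9.0% v 10.0% | 0.90 | 5.0% / 5.2% |
| 80% / 100% | 8.0% v 10.0% | 0.80 | 9.5% / 10.2% |
| 70% / 100% | 7.0% v 10.0% | 0.70 | 17% / 18% |

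In the opposite direction, 95% against 85% capture with no true effect gives 9.5/8.5 = 1.12, an apparent harm.

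A capture gap of about 10 points thus costs roughly 14 points of power, or doubles the chance of a false benefit. Larger gaps matter much more.

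**The case against.** The article takes real steps towards equal measurement: the same visit schedule, common documentation modules with plausibility checks, trained collectors and telephone follow-up in both arms. Outcome collection in the FLS-CARE arm is placed at the follow-up appointments, and nothing says that events learned of during home visits or coaching calls are counted. Treated fractures are also a fairly hard endpoint. All of this stands and lowers the likely size of any gap. It does not equalise who asks, how much other contact the patient has, or the recorder's stake in the result.

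Four stronger readings are tempting, and the document does not support them.

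- A reader might infer that claims are used only for process and cost outcomes. The article never excludes them for fractures, and Table 1, which may name sources, is not shown. What can be said is that the visible text assigns no arm-neutral source.
- A reader might infer that the statement about avoiding bias is simply wrong. Separate control staff plausibly limit contamination, the article's stated reason for randomising hospitals. The fair criticism is that separation does not protect measurement, and exchanges one risk for another.
- A reader might infer a bias in favour of FLS-CARE. The direction is not determined.
- A reader might infer that physicians are stated to be unblinded. The Allocation section names participants and nurses only; for physicians this follows from the non-blinded design and their part in the programme.

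Claims are no complete answer either. They miss falls that lead to no care and fractures that are never coded, and they can count repeat coding of the index fracture as a new one. The study was still in preparation, so linkage is planned and not yet shown to exist, and the article does not show whether consent covers this use.

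**Conclusion.** The point holds in this form: outcome collection, including fractures, is arm-specific and unblinded, lies partly with the staff who deliver the intervention, and has no stated arm-neutral source for the primary outcome. The stated safeguards reduce the risk of differential ascertainment without removing it.

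The sizes in the tables rest on assumed capture rates and on the protocol's ICC, cv and 507 per group. They show what a given gap would do, not that such a gap will occur. Falls depend on report and are more exposed than fractures, but they are a secondary outcome. Grade: should fix, with moderate confidence, because the full protocol or Table 1 may already name claims as the fracture source. In that case one sentence settles the matter for fractures.

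**What to change.** **Primary outcome.** Ascertain secondary fractures from the sickness-fund claims with one code list and one algorithm, applied in both arms without knowledge of arm. Include a rule that separates a new fracture from repeat coding of the index fracture, and censor at the end of insurance. A patient who misses visits then still contributes data while insured, which also helps with the loss expected among controls.

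**Supporting analysis.** Analyse nurse- and physician-recorded fractures separately and report their agreement with claims by arm. This would show any differential capture.

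**Falls.** Claims cannot capture falls without care. Count only answers to the same scripted question at t2, t3 and t4 in both arms.

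**Wording.** Present the separate control-arm staff as a measure against contamination, if that is the intent, and not as protection against measurement bias.

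**Cost.** Protocol and analysis-plan text, a code list, and confirmation that consent and data agreements cover this use of claims. Claims arrive later than visit data and miss uncoded fractures. Recruitment had not started at the date of the article, so at that point the change could be made before any outcome was recorded.

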### Data management

Acquisition and documentation of all study data are fully IT based. FLS-CARE uses a SAP Business By Design© platform on a cloud-based IT architecture in combination with clinical trial software provided by the software partners Arvato Systems and ID. This platform solution allows multicentric secure VPN online access for all participating study centres. Databases are run in level 2 certified data centres in Germany. Access to the FLS-CARE application follows strict data security levels for both study centres and the study team. All study forms follow the time points of the participant timeline (see Table 1) using context-specific documentation sheets for both the different time points of data collection and the different user groups. A wide range of software-based plausibility mechanisms is implemented into the documentation forms to define data values and allowed varieties of data entry for every single data field.

#### Confidentiality

Compliance with the legal provisions on data protection and data security within the framework of the FLS-CARE study will be guaranteed by the study group. The collection and processing of data is carried out under strict observance of the legal regulations, in particular the provisions of data protection, medical confidentiality and social secrecy. Decisive are sections 284 et seq*. Fünftes Sozialgesetzbuch* (SGB V) and §§ 67 and 67a *Zehntes Sozialgesetzbuch* (SGB X) on data collection, § 203 *Strafgesetzbuch* (StGB) in conjunction with § 9 *Muster-Berufsordnung für Ärzte* (MBO) on medical confidentiality, § 35 *Erstes Sozialgesetzbuch* (SGB I) on social secrecy and § 5 *Bundesdatenschutzgesetz* (BDSG) on data secrecy.

The data are only forwarded to GPs and medical specialists involved in the study or if the legislator allows the forwarding under defined conditions. The scientific and statistical evaluation of the data collected within the framework of the FLS-CARE study is carried out exclusively with pseudonymised data that preclude any inferences being drawn about the patients.

Data storage takes place in external, certified data centres in Germany. Access to the stored data is only possible by or on behalf of authorised persons.

### Statistical methods

Evaluation of the study will be performed as intention to treat analysis with patients as the unit of observation.

Although the stratification of the cluster aims at evenly distributed patient characteristics, it cannot guarantee perfect comparability of the two groups. Thus, the need for an adjusted model within the regression models is examined at the beginning of the analyses (e.g. due to unequal distribution of relevant baseline characteristics and risk factors). Mixed models are expected to be best fitting for analysing the secondary fracture rate over the study period of 2 years (primary outcome).

Secondary outcomes are descriptively summarised and, if appropriate, analysed within adjusted regression models depending on the type of variable, also considering potential cluster effects. Differences in mortality rates of the FLS-CARE and control group are estimated through survival analyses.

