## Methods

### Trial design

The study is set up as a non-blinded, cluster-randomised, controlled trial with unequal cluster sizes. Allocation to intervention group (FLS-CARE) and control group (usual care) follows an allocation ratio of 1:1 using hospitals (trauma centres) as the unit of allocation. In total, 18 study sites (9 hospitals per group) across Bavaria participated in the study. The cluster-randomised study design was chosen to avoid contamination bias by clinical staff and other patients within one centre.

For the purpose of this study, only trauma centres located in one federal state of Germany (Bavaria) are included.

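### The sample size makes no small-sample allowance for 9 hospitals per arm: on its own inputs a t test on 16 df has about 75% power, not 80%, and the primary test should name a small-sample reference

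*Protocol article*

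**What the plan says.** Trial design sets the number of randomised units: "In total, 18 study sites (9 hospitals per group) across Bavaria participated in the study". Allocation stratifies the hospitals by trauma-centre type and by metropolitan location.

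Sample size gives these inputs: "9 hospitals per group, an intra-cluster correlation of 1% and a coefficient of variation of clusters of 1.37 were assumed". With 3% secondary fractures expected under FLS-CARE and 10% under usual care, 80% power and a 5% significance level, it concludes that "507 patients are needed per group to find a significant difference of 7% in the secondary fracture rate". A 20% drop-out allowance raises this to 608 recruited per group. The section does not mention a t distribution or degrees of freedom.

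Recruitment intends an upper limit of 104 patients per hospital, open to minor adaptation because of the pandemic.

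Statistical methods says of the primary outcome: "Mixed models are expected to be best fitting for analysing the secondary fracture rate over the study period of 2 years". It names no link function, test, reference distribution or degrees-of-freedom method.

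**The concern.** Treatment is assigned to hospitals, so the evidence on its effect lies in the contrast between 9 hospitals and 9 others. That contrast carries about 18 − 2 = 16 degrees of freedom, and fewer once hospital-level factors are fitted. With so few, the between-hospital variance is poorly estimated and a normal reference is too generous.

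Two things follow. A power figure built on normal quantiles overstates what a properly calibrated test can deliver. And if the analysis used the same normal reference, a p-value just under 0.05 on the only primary hypothesis would not come from a 5% test.

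**Working it through.** **1. Reproduce 507.** Inputs from Sample size: p₁ = 0.10, p₂ = 0.03, k = 9, ρ = 0.01, cv = 1.37. Sidedness is not stated; two-sided is assumed here.

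Individually randomised size, pooled normal formula, with mean risk 0.065:

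n_i = [1.960·√(2·0.065·0.935) + 0.842·√(0.10·0.90 + 0.03·0.97)]² / 0.07² = 193.5, rounded up to 194.

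The printed cluster formula, with cv² + 1 = 2.8769:

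n_C = 194·9·0.99 / (9 − 194·2.8769·0.01) = 1728.54 / 3.419 = 505.6.

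With n_i = 194.2 it gives 507.0, and with 195 it gives 512.5. The other versions tried do not fit:

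| Version | n_i | n_C |
|---|---|---|
| one-sided | 153 | 296 |
| continuity-corrected | 222 | 757 |
| unpooled | 190.8 | 484 |
| arcsine | 180 | 420 |

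So 507 is a two-sided, pooled, normal-theory figure.

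**2. Power at 507 with a normal reference.** Effective size per arm is

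n_eff = N / {1 + [(cv² + 1)·N/k − 1]·ρ} = 507 / (1 + 161.07·0.01) = 194.2.

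The pooled standard error is √(0.12155/194.2) = 0.02502 and the unpooled one √(0.1191/194.2) = 0.02476.

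Power = Φ[(0.07 − 1.96·0.02502)/0.02476] = 80.1%, which matches the stated 80%.

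**3. Power at 507 with a t reference.** The critical value on 16 df is 2.120 instead of 1.960. The noncentrality is 0.07/0.02502 = 2.80 (2.83 unpooled). Noncentral-t power is 74.8% (75.6% unpooled), so about 75%. If each two-level stratification factor takes one degree of freedom, 14 remain and power is about 74%; on 13 it is 73.5 to 74.3%. Reaching 80% on 16 df with these inputs would need n_i of about 217 to 220, which the printed formula turns into about 696 to 731 analysed per arm.

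**4. Power under the recruitment cap.** If sizes lie between 0 and 104, the largest possible coefficient of variation is √(104/mean − 1). Taking 20% off the 608 recruited leaves 486 analysed, so both sizes are shown.

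| Basis for the mean | Mean per hospital | Maximum cv |
|---|---|---|
| 608 recruited | 67.6 | 0.73 |
| 507 analysed | 56.3 | 0.92 |
| 486 analysed | 54.0 | 0.96 |

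| Analysed per arm | cv | Power, t on 16 df |
|---|---|---|
| 507 | 0.73 | about 88% |
| 507 | 0.92 | about 85% |
| 486 | 0.73 | about 87% |
| 486 | 0.96 | about 83% |

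**5. Type I error if 1.96 were used as the cut-off.** If the statistic follows t on 16 df, P(|t| > 1.96) = 6.8%; on 13 df it is 7.2%. Simulated logistic mixed models with no treatment effect, 10% risk and ρ = 0.01 gave:

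| Setting | Wald z | t on 16 df |
|---|---|---|
| 487 per arm, 20 to 83 per hospital, 8000 runs | 7.0% | 5.2% |
| 507 per arm, cv 0.7, 1000 runs | 9.3% | 6.8% |
| 507 per arm, cv 1.37, 1000 runs | 10.5% | 7.8% |

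In the first setting an unweighted hospital-level t test gave 4.8%, and the hospital variance was estimated as zero in 26% of runs.

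**The case against.** A reader might infer two stronger claims: that the planned primary test is anticonservative, and that the trial is underpowered. The document supports neither.

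On the first, Statistical methods leaves the test open. A mixed model with a small-sample correction is as consistent with the text as a Wald z test. The choice is commonly left to the analysis plan, which is not shown. Silence on it is therefore no defect, and the type I error figures are conditional. They also vary with the size distribution and estimation choices, so they show direction rather than a firm value.

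On the second, the 75% depends on a coefficient of variation of 1.37, which the 104-patient cap rules out. Reaching 1.37 would need a cap of roughly 162 to 194, more than a minor adaptation. Within the cap, a t test on 16 df keeps more than 80% power.

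The 75% is also the plan's own sizing formula with a t reference, not a forecast for a fitted mixed model. In the 1000-run simulation at nominal cv 1.37, the mixed model with a t cut-off rejected in 89.6% of runs under 3% against 10%. Its type I error there was 7.8%, however, so that is not the power of a 5% test.

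What remains is narrower. The printed power does not follow from the printed inputs under a test calibrated for 18 hospitals, and that figure stands in the protocol itself.

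**Conclusion.** The point holds as a shortfall in the stated power on the stated inputs: about 75% instead of 80%, or about 74% on 13 to 14 degrees of freedom. The type I error risk holds only if the primary model is tested with an uncorrected normal reference.

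The result assumes a two-sided 5% test, the article's event rates and intra-cluster correlation, and 16 degrees of freedom (18 hospitals less 2 arms). The cost of moving to t is similar at other correlations: at cv 1.37 and 507 per arm, power falls from 92% to 89% at 0.005 and from 60% to 54% at 0.02.

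**What to change.** State that the primary treatment effect is tested, and its confidence interval formed, with a small-sample reference: t with hospital-level degrees of freedom (hospitals minus hospital-level parameters). Because t on 16 df did not fully restore 5% in every simulated setting, a hospital-level analysis or a permutation test over the stratified allocation is a useful optional sensitivity check.

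Restate power on the same basis: about 75% if 1.37 is kept, or about 83 to 88% if the coefficient of variation is limited to what the cap permits (0.73 to 0.96, with 486 to 507 analysed per arm).

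The cost is a sentence in the analysis plan, a restated power figure, and intervals wider by 2.120/1.960 = 1.08, about 8% (9 to 10% on 14 to 13 df). No extra hospitals or patients are needed as long as the cap broadly holds.
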